### Acceptability

*Acceptability* will be assessed by conducting semi-structured interviews with 15 adults with CP who participated in the online exercise programme using the theoretical framework of acceptability
^30^ to inform topic guides and data analysis. The seven component constructs that represent acceptability are detailed in
Table 2 and include: affective attitude, burden, perceived effectiveness, ethicality, intervention coherence, opportunity costs, and self-efficacy.
^31^

**Table 2. T2:** Theoretical framework of acceptability components.
^31^

Components	Description
Affective Attitude	How an individual feels about the intervention
Burden	The perceived amount of effort that is required to participate in the intervention
Ethicality	The extent to which the intervention has good fit with an individual’s value system.
Intervention Coherence	The extent to which the participant understands the intervention and how it works
Opportunity Costs	The extent to which benefits, profits or values must be given up to engage in the intervention.
Perceived Effectiveness	The extent to which the intervention is perceived as likely to achieve its purpose.
Self-Efficacy	The participant’s confidence that they can perform the behavior required to participate in the intervention.

Topic guides will be developed in collaboration with clinical expert team and PPI contributors including adults with CP. The topic guides will be piloted with at least two adults with CP. Adaptations will be made to ensure the interviews are accessible and inclusive. This may include providing the topic guide in advance, using alternative systems of communication (using images as prompts), and pictorial memory aids. We will also offer conducting the interviews over two or more segments to minimise fatigue. The interviews will be conducted in person, by telephone or by Microsoft Teams, based on participant preference. In person interviews will be conducted in a private, accessible and comfortable setting that is free from distractions and allows for privacy and confidentiality. Interviews will be audio-recorded and transcribed verbatim.

### Adaptability

Adaptability will be assessed by exploring the adaptability of the programme for associated impairments and mobility levels during the semi-structured interview.

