**Methods:**

This feasibility randomised controlled trial will recruit 60 adults with CP. Participants will be randomly assigned to either an eight-week online exercise intervention or a control group. The feasibility of the programme will be evaluated across five key domains: 1) demand as indicated by recruitment rate; 2) implementation as indicated by attendance; 3) practicality as indicated by number and type of adverse events; 4) adaptability, by examining how the programme accommodates varying levels of mobility and associated impairments; and 5) acceptability explored through semi-structured interviews with participants. To assess preliminary efficacy, the Patient-Reported Outcomes Measurement Information System (PROMIS) will be used to measure changes in physical, mental, and social functioning at baseline and post-intervention. Quantitative outcomes will be analysed using linear mixed models, and qualitative data will be analysed using framework analysis.

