### Randomisation

Following the baseline assessment, participants will be randomly allocated to either an intervention or control group in a 1:1 ratio. Stratification will be based on their mobility status: GMFCS Level I-III (with or without walking aids) and GMFCS Levels IV-V (who use wheelchairs). The random allocation will be generated by a computer in random permuted blocks of 2 or 4, and implemented automatically within REDCap (Research Electronic Data Capture). Allocation concealment will be ensured as the sequence is embedded within REDCap and not accessible to the research team prior to assignment.

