The programme will be delivered by a physiotherapist (post-doctoral research fellow) and a specialist personal trainer in exercise for long-term neurological conditions. The programme content was developed with input from physiotherapists and personal trainers with expertise in CP, and from the Public and Patient Involvement (PPI) contributors who are adults with CP. The exercise programme will be piloted with PPI contributors in advance of the intervention commencing: any necessary refinements will be made based on feedback received. This will include refinement of adaptations to support delivery across a range of abilities and needs. During the intervention, adaptations will be informed by participant feedback and session experience. All adaptations made during programme delivery (e.g., modifications to exercises, level of support, or delivery approach) will be documented prospectively by the researcher delivering the intervention. The researcher delivering the programme will review sessions, document adaptations and implement any necessary adaptations in subsequent group classes. These documented adaptations will inform ongoing refinement of the intervention, interpretation of feasibility outcomes, and future implementation.

Detailed intervention materials, including exercise and educational content, will be made available alongside the publication of the study findings, informed by the feasibility outcomes.

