## Data collection

### Outcomes

Six domains of an evidence-based framework for feasibility studies will be evaluated: demand, implementation, practicality, potential efficacy testing, adaptability and acceptability
^21^ (
Table 1). Each domain will be assessed using predefined metrics as outlined in
Table 1, including recruitment rate (demand), attendance and exercise completion (implementation), adverse events (practicality), qualitative interviews exploring acceptability and adaptability, and changes in physical, mental and social outcomes (potential efficacy). These findings will inform progression to a larger, fully powered trial.

**Table 1. T1:** CP-Excel outcomes.

Domain	CP-Excel Outcomes
Demand	Recruitment rate
Implementation	Fidelity to the programme: Attendance at each class and completion of the exercise programme
Practicality	Recording of adverse events
Adaptability	Semi-structured interviews with adults with CP
Acceptability	Semi-structured interviews with adults with CP
Potential efficacy	Physical, mental and social outcomes

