### Efficacy

Efficacy will be assessed by investigating changes in outcomes from baseline to 8-weeks (
Table 3). The Patient-Reported Outcomes Measurement Information System (PROMIS) will be used to measure changes in physical, mental, and social functioning at baseline and post-intervention.
^32^
^–^
^35^ PROMIS measures are standardised self-reported instruments assessing domains such as physical function, pain, fatigue, sleep, mental health, and participation, typically reported as T-scores, with the direction of scoring dependent on the domain. The Functional Mobility Scale (FMS) assesses mobility across different distances and use of assistive devices,
^36^ and will be collected at both baseline and 8-week follow-up to assess changes over time. These measures were selected due to their relevance to the intervention, feasibility for remote administration, and suitability for adults with CP. Both have established psychometric properties, including reliability and validity, and have been used in neurological populations.
^32^
^–^
^36^

**Table 3. T3:** Outcomes.

Outcome	Outcome measure
Mobility	Functional mobility scale ^36^
Physical function	PROMIS-Physical function-Short form 10a
Pain	Self-reported questionnaire
Pain intensity	PROMIS-Pain intensity form
Pain quality	PROMIS Neuropathic pain quality 5a PROMIS Nociceptive Pain quality 5a
Pain interference	PROMIS-Pain interference – Short Form-8a
Fatigue	PROMIS-Fatigue-Short form 13a (FACIT fatigue)
Sleep	PROMIS-Sleep disturbance-Short Form 4a
Self-efficacy for managing daily activities	PROMIS-Self-efficacy for managing chronic conditions-managing daily activities-Short Form 8a
Self-efficacy for managing emotions	PROMIS-Self-efficacy for managing chronic conditions-managing emotions-Short Form 8a
Depression	PROMIS-Emotional Distress – Depression-Short Form 8a
Participation in social roles and activities	PROMIS-Ability to participate in social roles and activities-Short Form 8a

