## Data analysis

### Quantitative data analysis

To determine the demand of the programme, descriptive statistics will be used to report the number and proportion of participants who responded to invitations, potentially eligible participants identified over a 3-month period who meet the inclusion criteria, who agree to participate in the study, excluded from the study and who drop-out during the study.

To determine the fidelity of the programme, descriptive statistics will be used to report the number of sessions attended by participants and those who completed the exercise contents.

As this is a feasibility study, analyses of outcomes will be exploratory and are not intended to provide definitive evidence of effectiveness. To determine potential efficacy, we will explore changes in outcomes over time. Continuous PROMIS outcomes will be analysed using linear mixed models to examine changes between groups over time. The Functional Mobility Scale (FMS), an ordinal measure, will be analysed descriptively and explored using appropriate non-parametric or ordinal methods where feasible. Outcomes will be interpreted descriptively in line with the feasibility design, with reference to established scoring approaches for PROMIS measures where available. Where data are missing, analysis will be conducted on available cases, and patterns of missingness will be explored descriptively. Multiple imputation methods will not be applied. STATA version 18 will be used for analysis.

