### Qualitative data analysis

Data from semi-structured interviews will be analysed through Framework analysis. Framework analysis is appropriate for this study as we have pre-defined components of acceptability (Sekhon
*et al.*, 2017) that we wish to explore but are also open to emergence of additional themes. Adaptability of the programme for associated impairments and mobility level will also be explored from this interview data. Participant experiences of both the exercise and health education components of the intervention, and their interaction, will also be explored.

Framework analysis involves seven iterative stages: Transcription, familiarisation, coding, developing a working analytical framework, applying the analytical framework, charting, and interpretation.
^37^ The post-doctoral research fellow will read a sample of transcripts until familiarity with the data is established. Then will independently develop provisional codes. The codes will be reviewed, discussed and refined in collaboration with the project management group (PMG), who will also read selected transcripts to support the development of a working analytical framework. Once the framework is established, the post-doctoral research fellow will apply it to all transcripts. Any issues arising during this process will be discussed with the PMG, before finalising the framework. Data will then be arranged into charts that summarise themes, issues and individual responses. Finally, the post-doctoral research fellow will present the emerging categories and themes to the advisory group and PPI for discussion. We will use strategies to enhance trustworthiness of the findings, such as negative case analysis, peer-debriefing and reflexivity. NVivo 12 Pro (Lumivero, Denver, CO, USA) will be used to support data management and analysis.

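### Adaptability across mobility levels is fixed as an interview-only outcome; the attendance, dose, safety and adaptation data already collected are neither assigned to it nor stated by GMFCS stratum

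*Protocol article*

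**What the plan says.** The abstract of the protocol article describes the domain as "adaptability, by examining how the programme accommodates varying levels of mobility and associated impairments". The trial admits adults at any GMFCS level (Participants), and randomisation is stratified into GMFCS I-III and IV-V (Randomisation).

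The measure is then given in several places, each time as interviews:
- Outcomes, among the predefined metrics: "qualitative interviews exploring acceptability and adaptability". The adaptability row of Table 1 lists semi-structured interviews and nothing else.
- Adaptability: "Adaptability will be assessed by exploring the adaptability of the programme for associated impairments and mobility levels during the semi-structured interview".
- Qualitative data analysis: "Adaptability of the programme for associated impairments and mobility level will also be explored from this interview data".

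The Acceptability section sets the interviews at 15 adults who took part in the online programme and does not mention GMFCS level. Under Risk assessment, which follows randomisation, people whose safety cannot be assured do not go on to the intervention.

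The other relevant data sit elsewhere. Attendance and completion belong to implementation, and adverse events to practicality (Table 1). For fidelity, Quantitative data analysis says that "descriptive statistics will be used to report the number of sessions attended by participants and those who completed the exercise contents". Sets and repetitions in supervised classes are recorded (Intervention group). On the log, the same section says: "All adaptations made during programme delivery (e.g., modifications to exercises, level of support, or delivery approach) will be documented prospectively". It adds that the log will inform refinement of the programme, interpretation of the feasibility outcomes in general, and future implementation.

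**The concern.** The adaptability question is whether one programme can serve people from GMFCS I to V and people with associated impairments. Interviews can show how adaptation was experienced. They cannot count who could not start, who stopped attending, or who managed fewer sets. Those counts, split by mobility stratum, are the most direct evidence, and the trial will hold them.

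The people eligible for interview also lean towards a favourable answer. Someone randomised to the programme but stopped at the risk assessment may be the clearest case of adaptation falling short, yet did not take part and so is outside the group described for interview.

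The Outcomes section says that the findings will inform progression to a larger trial. Whether that trial should take all GMFCS levels in one format depends on this domain. A programme that works poorly in IV-V could be reported as adaptable if overall attendance looks good and few interviewees come from that stratum.

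**Working it through.** **Inputs from the protocol article.** 60 participants at 1:1, so 30 per arm; 8 weekly classes; 15 interviews; strata GMFCS I-III and IV-V. The sample size has no formal power calculation, so there is no figure of the plan's own to reproduce.

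**Inputs assumed.** The share p of GMFCS IV-V in the intervention arm and the attendance rate in each stratum. The documents give neither, so a range is shown.

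**1. What is assigned to adaptability**

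| Data item | Domain in the plan | By stratum? |
|---|---|---|
| Interviews (15) | Adaptability, acceptability | Not stated |
| Attendance, home completion | Implementation | Not stated |
| Sets and repetitions | No domain named | Not stated |
| Adverse events | Practicality | Not stated |
| Adaptation log | Feasibility outcomes in general | Not stated |
| Starting after risk assessment | No domain named | Not stated |

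**2. What an overall attendance figure can hide**

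Overall attendance = (1 − p) × 0.85 + p × 0.40, with 85% in I-III (6.8 of 8 classes) and 40% in IV-V (3.2 of 8) assumed.
- p = 10% (3 people): 0.765 + 0.040 = 0.805, about 81%
- p = 20% (6 people): 0.680 + 0.080 = 0.760, or 76%
- p = 30% (9 people): 0.595 + 0.120 = 0.715, about 72%

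One stratum misses most classes while the overall figure stays above 70%.

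**3. How many interviewees would come from IV-V if stratum is ignored**

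With K people in IV-V among 30 and 15 drawn at random, P(X = k) = C(K, k) × C(30 − K, 15 − k) / C(30, 15).

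| K of 30 | Mean | P(at most 1) | P(at most 2) |
|---|---|---|---|
| 3 (10%) | 1.5 | 0.50 | 0.89 |
| 6 (20%) | 3.0 | 0.08 | 0.33 |
| 9 (30%) | 4.5 | 0.007 | 0.05 |
| 12 (40%) | 6.0 | 0.0002 | 0.004 |

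If K = 6 but 3 of them never start, 27 people remain, 3 of them in IV-V. The mean is then 15 × 3/27 = 1.7 and P(at most 1) = 0.41, against 0.08 when all six start.

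**4. Precision of a stratum result**

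Exact (Clopper-Pearson) 95% intervals: 3 of 6 gives 12-88%; 6 of 12 gives 21-79%.

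**The case against.** The strongest reply is that this is silence rather than error. Breakdowns by stratum and the choice of interviewees are often left to an analysis plan or full protocol that is not shown, and nothing in Quantitative data analysis rules out tables by GMFCS. That stands for the tables: a reader might infer that attendance will be reported only overall, but the text does not say so. It does not answer the point about the measure. Table 1, the Adaptability section and the qualitative analysis all tie the domain to interviews, so further tables would not count as adaptability evidence unless that definition changes.

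Second, the log is already linked, because it informs interpretation of the feasibility outcomes and adaptability is one of them. This stands in part. The log is not unused, and the plan as a whole is wider than the Table 1 row. It is still not named as an adaptability measure or tied to mobility level.

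Third, a reader might infer that the interviewees will be mainly ambulant. The documents do not support that. Fifteen is half of the arm, accessible interview formats are planned, and recruitment runs partly through a wheelchair users' organisation. The calculation agrees: thin representation is likely only if IV-V are about 20% of the arm or less, or if they fail to start more often.

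Fourth, a reader might extend the point to the Functional Mobility Scale, arguing that wheelchair users have little room to change on it. That rests on scoring details that the article does not give, and the scale belongs to potential efficacy. It forms no part of this point.

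**Conclusion.** The point holds as a weakness in a stated measure, not as a contradiction or a wrong figure. Adaptability is about mobility levels and impairments, but its only assigned measure is 15 interviews with people who took part. No spread over the strata is stated, and those stopped at the risk assessment are outside the group. The more direct evidence is collected but not assigned to the domain.

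The size depends on assumptions. With attendance of 85% and 40% in the two strata, overall attendance is 81%, 76% and 72% at IV-V shares of 10%, 20% and 30%. A random choice of interviewees gives a 50% chance of at most one from IV-V at a 10% share and a 33% chance of at most two at 20%, falling to 5% for at most two at 30%. A misleading conclusion is therefore a possibility, not a certainty. Because the remedy is almost free, it is worth making.

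**What to change.** In Table 1, Adaptability and Quantitative data analysis, define the domain as the interviews plus descriptive results by randomisation stratum (GMFCS I-III, IV-V) for:
- the number randomised to the programme who start it;
- attendance;
- weekly home completion;
- sets and repetitions in supervised classes;
- adverse events;
- the number and type of logged adaptations.

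In Acceptability, state that the 15 interviewees will be chosen so that both strata are represented.

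The cost is protocol wording and a few tables from data already collected; the sample size stays at 60. The drawback is precision. GMFCS IV-V may number only a handful (3 of 6 carries an interval of 12-88%), so the report should give counts, state the uncertainty, and make no between-stratum tests.

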### Efficacy

Efficacy will be assessed by investigating changes in outcomes from baseline to 8-weeks (
Table 3). The Patient-Reported Outcomes Measurement Information System (PROMIS) will be used to measure changes in physical, mental, and social functioning at baseline and post-intervention.
^32^
^–^
^35^ PROMIS measures are standardised self-reported instruments assessing domains such as physical function, pain, fatigue, sleep, mental health, and participation, typically reported as T-scores, with the direction of scoring dependent on the domain. The Functional Mobility Scale (FMS) assesses mobility across different distances and use of assistive devices,
^36^ and will be collected at both baseline and 8-week follow-up to assess changes over time. These measures were selected due to their relevance to the intervention, feasibility for remote administration, and suitability for adults with CP. Both have established psychometric properties, including reliability and validity, and have been used in neurological populations.
^32^
^–^
^36^

**Table 3. T3:** Outcomes.

Outcome	Outcome measure
Mobility	Functional mobility scale ^36^
Physical function	PROMIS-Physical function-Short form 10a
Pain	Self-reported questionnaire
Pain intensity	PROMIS-Pain intensity form
Pain quality	PROMIS Neuropathic pain quality 5a PROMIS Nociceptive Pain quality 5a
Pain interference	PROMIS-Pain interference – Short Form-8a
Fatigue	PROMIS-Fatigue-Short form 13a (FACIT fatigue)
Sleep	PROMIS-Sleep disturbance-Short Form 4a
Self-efficacy for managing daily activities	PROMIS-Self-efficacy for managing chronic conditions-managing daily activities-Short Form 8a
Self-efficacy for managing emotions	PROMIS-Self-efficacy for managing chronic conditions-managing emotions-Short Form 8a
Depression	PROMIS-Emotional Distress – Depression-Short Form 8a
Participation in social roles and activities	PROMIS-Ability to participate in social roles and activities-Short Form 8a

## Data analysis

### Quantitative data analysis

To determine the demand of the programme, descriptive statistics will be used to report the number and proportion of participants who responded to invitations, potentially eligible participants identified over a 3-month period who meet the inclusion criteria, who agree to participate in the study, excluded from the study and who drop-out during the study.

To determine the fidelity of the programme, descriptive statistics will be used to report the number of sessions attended by participants and those who completed the exercise contents.

As this is a feasibility study, analyses of outcomes will be exploratory and are not intended to provide definitive evidence of effectiveness. To determine potential efficacy, we will explore changes in outcomes over time. Continuous PROMIS outcomes will be analysed using linear mixed models to examine changes between groups over time. The Functional Mobility Scale (FMS), an ordinal measure, will be analysed descriptively and explored using appropriate non-parametric or ordinal methods where feasible. Outcomes will be interpreted descriptively in line with the feasibility design, with reference to established scoring approaches for PROMIS measures where available. Where data are missing, analysis will be conducted on available cases, and patterns of missingness will be explored descriptively. Multiple imputation methods will not be applied. STATA version 18 will be used for analysis.

